## **D. Study Sites**

### **D.1. Overview**

20 Wisconsin NHs, purposively selected for their geographic location to achieve a balance between rural and urban facilities, will be selected for participation in this study. Our rationale for employing this sampling approach is that rural NHs are less likely to be members of a NH network and may have more limited access to improvement resources and expertise. This approach will enhance our capacity to identify barriers to implementation that will be encountered in NHs throughout Wisconsin and enhance future toolkit dissemination efforts.

#### **D.1.1. Inclusion criteria**

- a) Medicare and Medicaid (dually) certified nursing homes
- b) Long-term care and skilled nursing beds > 50 beds
- c) The management of the facility agrees to random allocation to control or intervention group
- d) The facility is able to submit 3 sequential months of data on facility urine culture and antibiotic treatment rates via the study web portal

#### D.1.2. Exclusion criteria

- a) Assisted living facility wards
- b) Specialty care (ventilator or strict rehabilitation) wards

#### D.2. Recruitment

Facilities have been recruited through referrals from members of the Wisconsin Healthcare-Associated Infections in Long-Term Coalition as well as Wisconsin nursing home associations (Leading Age and Wisconsin Health Care Association).

#### D.3. Randomization

Randomization will be computer generated and stratified based on geographic location (urban vs. rural) in block sizes of two.

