### **III. Study Methods**

#### **A. Overall Study Design and plan**

We will introduce the Wisconsin UTI Improvement Toolkit (see Section III.B. Wisconsin UTI Improvement Toolkit) in 20 Wisconsin NHs and assess its impact on antibiotic utilization using segmented regression. Two different implementation strategies (see Section III.C. Study Arms) will be employed during the introduction of the Wisconsin UTI Improvement Toolkit in study NHs using a hybrid type 2 effectiveness-implementation study design in which half of the NHs will be randomized to usual (internally-driven) implementation with the other half randomized to externally-facilitated implementation based on coaching and peer-to-peer learning. The effects of the two implementation approaches will be assessed using a mixed methods approach.

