##### **C.2. Intervention Arm: Externally-facilitated implementation**

NHs randomized to the externally-facilitated arm will attend the same kickoff meetings and have access to the same online resources as the control arm but will also be assigned a clinical coach and will have the opportunity to participate in a series of hosted peer-to-peer learning opportunities. The clinical coach will meet regularly with NH staff to guide the facility through implementation of the Wisconsin UTI Improvement Toolkit. Coach supports will occur during a site visit and individual coaching calls.

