### E.2.3. Facility Demographics

A variety of facility-level demographic data will be collected in order to assess comparability between control and intervention facilities. These will include:

- a) Geographic location (rural versus urban)
- b) Size (beds)
- c) Skilled nursing services provided (e.g., parenteral therapy, wound care, etc)
- d) Ratio of skilled to domiciliary care beds
- e) Resident complexity (Resource utilization group [RUG])
- f) Staffing ratios (registered nurse [RN], licensed practical nurse [LPN], certified nursing assistant [CNA])
- g) Staff turnover (RN, LPN, CNA)
- h) Existing facility antibiotic stewardship structure and process
- i) Organizational culture
- j) Nursing home quality measures

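### Aim 2 only: the 20 homes are allocated without using the baseline rates that eligibility calls for; ordering homes by baseline rate before the same blocks of two would cheaply sharpen the arm comparison

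*Protocol*

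**What the plan says.** - **Allocation (D.3):** "Randomization will be computer generated and stratified based on geographic location (urban vs. rural) in block sizes of two". This is the only rule given. The order in which homes fill the blocks is not stated.
- **Number of homes (D.1, A):** "20 Wisconsin NHs, purposively selected for their geographic location to achieve a balance between rural and urban facilities"; "half of the NHs will be randomized to usual (internally-driven) implementation with the other half randomized to externally-facilitated implementation". That makes 10 homes per arm.
- **Baseline data (D.1.1, criterion d):** "The facility is able to submit 3 sequential months of data on facility urine culture and antibiotic treatment rates via the study web portal". These rates correspond to the two primary measures in E.2.1. The protocol does not say whether the months are submitted before allocation.
- **Recruitment and start (D.2, C.2):** "Facilities have been recruited through referrals from members", in the past tense. Homes in the facilitated arm "will attend the same kickoff meetings" as the control homes.
- **Comparability (E.2.3):** "A variety of facility-level demographic data will be collected in order to assess comparability between control and intervention facilities". The ten items (a) to (j) do not name the baseline culture or UTI treatment rate.
- **Arm comparison (E.4, F.5):** the segmented Poisson model is extended by a covariate for arm, coded 0 or 1. Further control variables are to be explored only if home characteristics, such as size and staffing, turn out significantly imbalanced.

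**The concern.** A home's own past rate is likely to be the best available predictor of its later rate. The protocol links that information to eligibility but does not use it when forming the blocks. With 10 homes per arm, urban/rural stratification alone leaves the arms free to start at different levels on the primary measures.

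The stated arm analysis makes this matter. With a single arm covariate and no baseline-rate or arm-by-period term, any difference in starting level is part of the arm coefficient. The stated safeguard is weak here: with 10 homes per arm, a significance test will miss imbalances large enough to matter, and the baseline rate is not among the examples given. What is at stake is the precision of the test of hypothesis 2 (less inappropriate antibiotic use with external facilitation).

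**Working it through.** **1. The plan's own figure.** E.4 states 90% power for a 15% reduction from about 4.0 starts per 1,000 resident-days. For a before/after Poisson log rate ratio,

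power = Φ(|ln 0.85| / √(φ(1/E₁ + 1/E₂)) − 1.96), with E₂ = 0.85·E₁.

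Resident-days, months per period, alpha and overdispersion φ are not given, so the 90% can be neither reproduced nor refuted. At an assumed two-sided alpha of 0.05 and φ = 1 it needs E₁ = (1 + 1/0.85) / (0.1625/3.2415)² ≈ 866 starts before implementation, or 866/4 × 1,000 ≈ 216,000 resident-days per period. Fifteen homes of 75 beds over 6 months give 88.4%; with φ = 2 they give 61%. This figure concerns all homes pooled, so allocation does not enter it.

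**2. Inputs for the arm comparison.**
- From the protocol: 20 homes, 1:1, urban/rural strata, blocks of two, three baseline months, rate 4.0, more than 50 beds.
- Assumed: 10 urban and 10 rural homes, 51–150 beds, 85% occupancy, 12 post-implementation months, log-normal home rates with SD 0.2, 0.3 or 0.4 on the log scale, Poisson counts, and a home-specific change with SD 0.10.
- Yardstick: a ratio beyond 1/0.85 = 1.18, that is |log ratio| > 0.1625. The protocol's 15% is a before/after effect; it serves here only as a scale, since no between-arm effect is given.

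**3. Hand check of the starting gap.** An average home has 100.5 beds × 0.85 × 91.2 days ≈ 7,790 resident-days in three months, so about 31.2 starts. The variance of its observed log rate is SD² + 1/31.2 = SD² + 0.032. For 10 homes against 10, the SD of the log ratio is √(0.2 × (SD² + 0.032)).

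| Between-home SD | SD of log ratio | 0.1625 / SD of log ratio | Two-sided chance |
|---|---|---|---|
| 0.2 | 0.120 | 1.35 | 18% |
| 0.3 | 0.156 | 1.04 | 30% |
| 0.4 | 0.196 | 0.83 | 41% |

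**4. Simulation of the starting gap.** Blocks of two in arbitrary order were compared with blocks of two after sorting on the observed three-month rate within stratum.

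| Between-home SD | As written | Sorted first |
|---|---|---|
| 0.2 | about 19% | 0.4% |
| 0.3 | about 32% | 4% |
| 0.4 | about 44% | 11% |

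A separate simulation with 75 occupied beds per home and between-home CV 0.2, 0.3 and 0.4 gave 19%, 31% and 41% as written, against 0.1%, 1.4% and 6% paired. The observed gap includes count noise. For the underlying rates at SD 0.3 the chances are about 25% and 8%.

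**5. What this does to the arm estimate (SD on the log scale, between-home SD 0.3).**

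| Estimate of the arm effect | As written | Sorted first |
|---|---|---|
| Arm log rate ratio, no baseline term | 0.151 | 0.099 |
| Between-arm difference in change | 0.102 | 0.094 |
| The same, if high-rate homes fall more (assumed slope 0.3) | 0.111 | 0.086 |
| Adjusted for baseline rate | 0.099 | 0.097 |
| Adjusted for baseline rate, slope 0.3 | 0.084 | 0.081 |

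The first row is a fall of about one third (0.052/0.151 = 34%). The second is 8% (0.008/0.102) and the third 23% (0.025/0.111). With baseline adjustment little remains. In all cases the estimate averages to zero when there is no arm effect.

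**The case against.** The strongest reply is that nothing here is wrong. Stratified blocked randomisation is valid, and sorting on baseline is a refinement. The starting gap is also not the error that matters most in a design with a pre-period: for a comparison of change the gain is about 8%, and adjusting the model for the baseline rate without re-sorting does as well or slightly better (0.084 against 0.086 with the slope). The arm-by-period terms may stand in an analysis plan that is not shown. All of this stands. It limits the point to a cheap gain for the arm comparison as the protocol states it.

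The criticism of E.2.3 is also a small one. The list is of facility demographics, item (j) covers quality measures, and the quality indicators in E.1 include UTI prevalence.

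Stronger readings are tempting but not supported:
- A reader might infer that homes are paired by date of entry. D.3 does not say so, and D.2 suggests that the homes may be known in advance.
- A reader might infer that every home's rates are in hand at allocation. Criterion (d) speaks of ability to submit, gives no timing, and refers to antibiotic treatment rates without naming UTI starts.
- A reader might infer that the arm comparison is biased, or that a comparison of change is systematically distorted. It is not: the imbalance is due to chance and adds variance.
- A reader might set the imbalance against the 90% power. That figure belongs to the pooled before/after analysis.

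**Conclusion.** The point holds as a cheap improvement for Aim 2, not as an error. Under the arm model stated in E.4 and F.5, using the baseline rate in the allocation would cut the SD of the arm log rate ratio from about 0.15 to 0.10 at an assumed between-home SD of 0.3. It would also make a starting gap above 15% uncommon (4% instead of about 32%). The benefit shrinks to a few per cent if the arm comparison is one of change, and nearly vanishes if the baseline rate is adjusted for.

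The sizes rest on a between-home spread, home sizes, occupancy and follow-up length that the protocol does not give. Over SD 0.2 to 0.4 the chance of such a gap as written runs from about 19% to 44%. Feasibility rests on the three months being submitted before allocation, which is the normal order for an eligibility criterion but is not stated.

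**What to change.** 1. State in D.3 when the three months are submitted relative to allocation, and how homes are ordered within the blocks.
2. Once all three baseline months are in, randomise all homes together. Within urban and rural, order homes by submitted baseline UTI treatment rate, then apply the existing blocks of two down that list.
3. Add the baseline urine culture and UTI treatment rates to the comparability measures in E.2.3.
4. If allocation in one batch is not feasible, adjust the arm model for the baseline rate, specified in advance and not conditional on a significance test. This recovers most of the same gain. It is worth doing with the sorted allocation too, because otherwise the standard error need not reflect the improved balance.

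The cost is one sort before the same computer-generated list is applied. The downside is that allocation, and so the start, waits for the last home's third month.

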### E. Study Outcomes

#### E.1. Overview

While the individual components of the Wisconsin UTI Improvement Toolkit are evidence-based, their combined effects on antibiotic prescribing are not known. We will assess the combined effects of the toolkit by comparing UTI treatment rates in study NHs before and after implementation of the toolkit using segmented regression methods. A number of data measures will be employed during this study.

| Focus Area                  | Domain                 | Measure(s)                                             | Data Source              |
|-----------------------------|------------------------|--------------------------------------------------------|--------------------------|
| Nursing Home Level Measures | Facility demographics  | Facility demographics (location, size, services, etc.) | UW NH Org Profile        |
|                             |                        | Resident characteristics (%post-acute, payer, etc.)    | CASPER database          |
|                             |                        | Nursing staffing levels (CNA, LPN, RN)                 |                          |
|                             |                        | Nursing retention measures                             |                          |
|                             | Work system            | People, tools, tasks, environment                      | Interviews & observation |
|                             |                        | Process and information flow maps                      |                          |
|                             |                        | ASP Structure and Process                              | UW ASP Survey            |
|                             | Organizational culture | Readiness for change                                   | UW organizational survey |
|                             |                        | Management support of frontline staff                  |                          |
|                             |                        | Perceived capacity to sustain change                   |                          |
| NH Level Measure            | Reach                  | # of NHs adopting the UTI toolkit with fidelity        | Interviews and surveys   |
|                             |                        | AS & DOT for UTI per 1,000 resident-days               | Facility supplied        |

|                                 |                                     |                                                                                                   |                                       |
|---------------------------------|-------------------------------------|---------------------------------------------------------------------------------------------------|---------------------------------------|
| Resident Level Outcomes         | Antibiotic measures (Effectiveness) | FQ-AS and FQ-DOT per 1,000 resident-days                                                          |                                       |
|                                 |                                     | % of AS for UTI meeting appropriateness criteria                                                  |                                       |
|                                 |                                     | % urine cultures positive for resistant bacteria                                                  |                                       |
|                                 |                                     | Number of positive Clostridium difficile tests                                             |                                       |
|                                 | Testing measures (Effectiveness)    | Urine cultures per 1,000 resident-days                                                            | Facility supplied                     |
|                                 |                                     | % of urine cultures meeting appropriateness criteria                                              |                                       |
|                                 | Safety measures                     | Hospital/ED transfers per 1,000 resident-days                                                     | Facility supplied                     |
|                                 |                                     | Resident deaths per 1,000 resident-days                                                           |                                       |
| Nursing Home Quality Indicators | Quality indicators (Effectiveness)  | Residents with UTI; Prevalence of UTI infection (only) and all infections                         | CHSRA/DHS Nursing Home Scorecard      |
|                                 | F-Tag Citations (Effectiveness)     | F-Tag 441 (Infection Control) and F-Tag 329 (Drug Regimen) as well as severity                    | CASPER                                |
| Staff Feedback                  | Adoption                            | Knowledge, attitudes, & perceptions about the toolkit
Participant feedback on implementation.  | Interviews and surveys                |
| NH and Staff Feedback           | Implementation                      | UTI toolkit fidelity checklist
Implementation Barriers and Facilitators                        | Interviews and surveys                |
| Maintenance                     | Resident and quality indicators     | Sustainability facilitators/barriers
Short-term sustainment of clinical indicator improvements | Interviews and Effectiveness Outcomes |

## E.2. Study Measures

### E.2.1. Primary Measures

- Urine culture orders per 1,000 resident-days.
- Antibiotic starts for treatment of suspected UTI per 1,000 resident-days.

### E.2.2. Secondary Measures

- Days of therapy for treatment of suspected UTI per 1,000 resident-days.
- Fluoroquinolone antibiotic starts and days of therapy per 1000 resident-days.
- Percentage of antibiotic starts for UTI meeting Wisconsin appropriateness criteria.
- Percentage of urine cultures meeting Wisconsin appropriateness criteria.
- Percentage of urine cultures positive for resistant bacteria.
- Number of positive *clostridium difficile* tests.
- Number of transfers to hospitals or emergency departments per 1000 resident-days.
- Number of resident deaths per 1000 resident-days.

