#### **B. Wisconsin UTI Improvement Toolkit**

The PI ([name]) has worked with academic, community and public partners in Wisconsin to develop a multi-component toolkit to improve the management of UTIs in NHs. The WI Healthcare Associated Infections (HAI) in Long term care (LTC) UTI toolkit was developed through a rigorous review of published theory and evidence [7] with input from frontline clinicians who practice in Wisconsin NHs and is structured around a UTI management framework developed by the PI [31]. The toolkit targets three major nursing staff and provider behaviors: (a) standardization of the assessment of the resident experiencing a change-in-condition; (b) implementation of delayed testing and treatment of residents experiencing a low-risk change-in-condition; and (c) appropriate selection of antibiotics (drug, dose, duration) in those residents where the likelihood of UTI is high. Education, communication, and decision-support tools have been developed in order to achieve improvements in each of these behavioral domains, and the toolkit also includes recommended practices to help prevent UTIs as well as process and outcome tracking tools designed to help staff in NHs assess implementation progress. Further details about the UTI toolkit are provided in the Appendix.

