#### **E.3.2. Secondary Outcome Measures**

Participating NHs will submit data on the number of urine cultures and antibiotic starts meeting Wisconsin appropriateness criteria [cite] via a web-based portal on a monthly basis. The Wisconsin appropriateness criteria [cite] require residents to either exhibit symptoms that localize to the urinary tract (e.g., dysuria, frequency) or systemic signs of infection (e.g., fever, hypotension, etc.) in the absence of another obvious source of infection.

The research team will obtain aggregate data on antibiotic prescriptions from the facility consultant pharmacy in order to determine days of antibiotic therapy per 1,000 resident-days as well as the number of fluoroquinolone starts and days of fluoroquinolone antibiotic therapy.

The research team will obtain aggregate data on urine culture results to determine the rates of urine culture resistance in study nursing homes. *Clostridium difficile* results at a facility level will be obtained in a similar manner.

Facilities will be asked to provide their aggregate resident transfer and mortality data on a monthly basis.

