#### **E.4. Data Analyses**

Generalized estimating equations using segmented regression and a Poisson distribution accounting for clustering by facility will be employed to evaluate the two primary outcomes across all study sites in aggregate. Four estimates from these models will be evaluated: 1) the pre-intervention trend ( $\beta_1$ ); 2) the immediate change in the outcomes following the kickoff webinar ( $\beta_2$ ); 3) the difference between pre- and post-implementation trend ( $\beta_3$ ); and 4) the post-implementation outcome rate change ( $\beta_1 + \beta_3$ ). First and second order autocorrelation will be assessed using the Durbin-Watson statistic. Robust standard errors will be used to estimate variance. Similar generalized linear models will be fit to analyze secondary and safety outcomes. To assess the impact of enhanced implementation on the effectiveness of the toolkit, the segmented regression model developed will be extended to include a covariate for the study implementation arm (control arm = 0; intervention arm = 1). We will explore adding control variables into our models if significant imbalances in NH characteristics (e.g., size, staffing ratios) are identified in our preliminary analyses. Based on data previously collected by our group [6], the expected rate of UTI treatment is ~4.0 per 1,000 resident-days. Assuming implementation of the UTI Toolkit leads to at least a 15% reduction in the UTI treatment rate and the facility dropout rate is <25%, our study will have 90% power to detect a statistically significant difference of this magnitude.

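### As defined, the resistance percentage can rise merely because low-yield urine cultures are avoided, and the C. difficile count lacks a resident-day denominator

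*Protocol*

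**What the plan says.** **Resistance.** Protocol III.E.2.2 lists the "Percentage of urine cultures positive for resistant bacteria". The measures table in III.E.1 has the same wording, as a percentage of "urine cultures positive for resistant bacteria". III.E.3.2 adds only this: "The research team will obtain aggregate data on urine culture results to determine the rates of urine culture resistance in study nursing homes". It names neither numerator nor denominator, so nothing narrows the literal reading that all cultures are the base.

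**What the toolkit acts on.** One of its three target behaviours (III.B) is "implementation of delayed testing and treatment of residents experiencing a low-risk change-in-condition". Module 3 in the Appendix gives nursing staff scripted language to the same end. The first primary measure (III.E.2.1) is "Urine culture orders per 1,000 resident-days".

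**C. difficile.** III.E.2.2 lists the "Number of positive *clostridium difficile* tests", and the III.E.1 table agrees. Neither gives a denominator. The item for deaths in the same list reads "Number of resident deaths per 1000 resident-days". Cultures, antibiotic starts, days of therapy and transfers are also expressed per 1,000 resident-days.

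**Analysis.** III.E.4 says that secondary and safety outcomes will be analysed with generalized linear models like those for the primary outcomes, which are Poisson segmented regressions fitted by GEE with clustering by facility. It mentions no offset or exposure term.

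**The concern.** A resistance percentage over all cultures is the product of two things: the share of cultures that are positive, and the share of positives that are resistant. Only the second is resistance. The intervention is built to change which residents are cultured, and so can change the first. If low-risk residents' cultures are positive less often, a toolkit that works as intended could appear to worsen resistance. Section II also hypothesises better adoption in the externally facilitated arm, so any such artefact could differ between arms.

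A bare count of positive C. difficile tests scales with the resident-days behind it. Homes need only exceed 50 beds (III.D.1.1), so exposure will differ between homes, and census can change over time.

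Both measures sit among the Resident Level Outcomes, which F.4.2 and F.4.5 reuse for the Effectiveness and Maintenance parts of the RE-AIM evaluation. The definitions therefore carry forward into those summaries.

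**Working it through.** The protocol gives no figure for either outcome, so there is none to reproduce. Its only power figure (90%) concerns the UTI treatment rate and plays no part here. Culture yields, the resistant share, census and period lengths below are all assumptions.

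**1. Resistance, yield artefact.** Take 100 cultures before the toolkit: 50 in high-risk residents with a yield of 60%, and 50 in low-risk residents with yield y. Let 30% of positives be resistant in both groups throughout. The toolkit removes 30 low-risk cultures, leaving L = 20 in place of L = 50.

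Percentage of all cultures = 0.30 × (50 × 0.60 + L × y) / (50 + L)

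| Low-risk yield y | Before (L = 50) | After (L = 20) | Change |
|---|---|---|---|
| 20% | 0.30 × 40/100 = 12.0% | 0.30 × 34/70 = 14.6% | +2.6 points |
| 30% | 0.30 × 45/100 = 13.5% | 0.30 × 36/70 = 15.4% | +1.9 points |
| 40% | 0.30 × 50/100 = 15.0% | 0.30 × 38/70 = 16.3% | +1.3 points |
| 60% | 0.30 × 60/100 = 18.0% | 0.30 × 42/70 = 18.0% | 0 |

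With positive cultures as denominator the value is 30% in every cell. The driver is the yield gap, not the number of cultures: with equal yields, removing 30 of 100 cultures changes nothing. A smaller gap gives a smaller shift. With y = 50% and 25 low-risk cultures removed, the percentage goes from 0.30 × 55/100 = 16.5% to 0.30 × 42.5/75 = 17.0%.

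**2. Resistance, what the redefinition leaves.** Now let positives be 35% resistant in high-risk and 25% in low-risk residents, with yields of 60% and 30% and the same removal of 30 low-risk cultures.

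- Resistant positives before: 0.35 × 30 + 0.25 × 15 = 14.25. After: 0.35 × 30 + 0.25 × 6 = 12.0.
- Over positive cultures: 14.25/45 = 31.7% to 12.0/36 = 33.3%, a shift of 1.7 points.
- Over all cultures: 14.25/100 = 14.3% to 12.0/70 = 17.1%, a shift of 2.9 points.

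The positive-culture denominator removes the yield artefact but not all selection.

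**3. C. difficile.** Expected count = rate × resident-days. At one constant rate:

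- Two homes with a census of 50 and 100, observed for the same month, have expected counts in the ratio 100/50 = 2.0.
- If census falls by some fraction, the expected count falls by the same fraction.
- Totals over 3 months before and 9 months after have the ratio 9/3 = 3.0; over 6 and 12 months, 12/6 = 2.0.

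The corresponding ratio of rates per resident-day is 1.00 in each case.

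**The case against.** The best defence is that III.E.4 already leads to the right analysis for C. difficile. III.E.3.2 obtains the results by facility, and a model like the primary one could carry a resident-day offset, a detail that a protocol often leaves to the SAP. Such an offset would remove most of the exposure problem. That stands, but the protocol defines this outcome as a number while defining its neighbours as rates, so nothing in it asks for the offset. An offset would also do nothing for the resistance denominator.

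The defence is also right that the resistance shift rests wholly on assumed yields, that it can be small, and that the proposed redefinition is not free of selection (step 2).

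Several stronger readings are tempting, and the documents do not support them:

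- *The measures track testing or attrition instead of resistance or infection.* Both also respond to true change.
- *Dropout shifts the resistance percentage.* It does not do so mechanically if the homes that leave resemble those that stay.
- *Testing volume drives the C. difficile count.* Nothing in the protocol says that the toolkit changes C. difficile testing; its targets concern urine testing and the treatment and prevention of UTI.
- *The C. difficile count would fall by a quarter through attrition.* The condition that "the facility dropout rate is <25" per cent is an assumption in the power statement, not a forecast. In a facility-level model, a home that leaves stops contributing observations and does not lower the counts of the others.
- *Facility size biases the before-after comparison.* A fixed size difference creates no change over time. For the arm comparison, III.E.4 names size as a possible control variable.

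**Conclusion.** The point holds as a defect in how two secondary outcomes are defined.

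For resistance, the all-cultures percentage rises by about 1 to 3 points with resistance among positives unchanged. This assumes high-risk yield of 60%, low-risk yield of 20% to 40%, a constant 30% resistant share, and avoidance of low-risk cultures equal to 30% of all cultures. The rise shrinks as the yield gap closes and vanishes when yields are equal. The protocol gives no yields, so the size in these homes is unknown.

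For C. difficile, the count as defined mixes infection with census, facility size and months observed. An offset would deal with most of this but is not stated.

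Neither primary measure nor the power statement is affected. This is a low-severity point, worth making because the correction is nearly free.

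**What to change.** In III.E.1 and III.E.2.2:

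- Define the resistance outcome as the percentage of **positive** urine cultures yielding resistant bacteria.
- Define the C. difficile outcome as positive tests per 1,000 (or 10,000) resident-days, and state that it is modelled with a log resident-days offset.

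The cost is mainly wording. Aggregate urine culture and C. difficile results are already to be obtained (III.E.3.2), and resident-days are needed for the other rates. The culture data must report positive cultures and resistant positives separately.

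There are two downsides. The positive-culture denominator is smaller, so the percentage is somewhat less precise. It can also still shift with testing if resistance differs between positives from low-risk and high-risk residents, and this caveat should accompany the result.
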